**Table 4 Key indicators targeting MSM used by FHI, UNAIDS, and PEPFAR for behavioral surveillance purposes.**

| Cascade Step      | Indicator                                                                                                                                   | Indicator # | Measure                                                                                                                                                    |
|--------------------------|----------------------------------------------------------------------------------------------------------------------------------------------------|--------------------|-------------------------------------------------------------------------------------------------------------------------------------------------------------------|
| Identify population size | Estimated total number of key populations in the program geographic area (denominator for KP_PREV)                                                 | PMP 1.1b (denom.)  |                                                                                                                                                                   |
| Reach people, Coverage   | Percentage of people from key population who have received free condoms and lubricant in the past 12 months                                        | WHO CCP-3, CCP-5   | Num: Number of respondents who received free condoms and lubricant in the past 12 months

Denom: Number of people interviewed                               |
|                          | Percentage of respondents who have been tested for HIV during the last 12 months and who know their results (prior to participation in the survey) | GARPR 1.9 & 1.13   | Numerator: Number of respondents who have been tested for HIV during the last 12 months and who know the results.

Denominator: Total number of respondents |

Programmatic Mapping and HIV/STI Prevalence Study among Key Populations in Angola

| Cascade Step | Indicator                                                                                                                                                                                                   | Indicator #          | Measure                                                                                                                                                                                                                                         |
|--------------|-------------------------------------------------------------------------------------------------------------------------------------------------------------------------------------------------------------|----------------------|-------------------------------------------------------------------------------------------------------------------------------------------------------------------------------------------------------------------------------------------------|
|              | Percentage of people from key population who have been screened for STI in the past 12 months (prior to participation in the survey)                                                                        | WHO SRH-4            | Num: Number of respondents who have been screened for STI in the past 12 months

Denom: Number of people interviewed                                                                                                                      |
|              | Percentage of people from key population who have received information on HIV, AIDS, condoms or safe sex in the past 12 months (from an outreach or health worker)?                                         |                      | Num: Number of respondents who have received information on HIV, AIDS, condoms or safe sex in the past 12 months?

Denom: Number of people interviewed                                                                                    |
|              | Key population reporting they have received a combined set of health sector interventions                                                                                                                   | WHO PKG-2            | Condoms; lubricant; information on condom use and safe sex; HTC; STI screening;                                                                                                                                                                 |
|              | Proportion of key populations reached with individual and/or small group level HIV preventive interventions that are based on evidence and/or meet the minimum standard required (KP_PREV/CUSTOM INDICATOR) | PMP 1.1b             | Num: Number of respondents who have received any of the above interventions in the past 12 months

Denom: Number of people interviewed                                                                                                    |
|              | Percentage of people from key population reached with HIV prevention programs                                                                                                                               | GARPR 1.7, 1.11, 2.1 | Participants who respond, 'Yes' to the following questions:

1. Do you know where you can go if you wish to receive an HIV test?

2. In the last 12 months, have you been given condoms?

Denom: Number of people interviewed |
| Test people  | Proportion of key populations who received HIV testing and counseling services for HIV and received their test results (HTC-3, GARPR 1.9, 1.13 & 2.4)                                                       | 1.3b                 | Num: Number of people tested for HIV who receive their results

Denom: Estimated number of key population living with HIV in the program geographic area                                                                                  |

Programmatic Mapping and HIV/STI Prevalence Study among Key Populations in Angola

| Cascade Step         | Indicator                                                                | Indicator #            | Measure                                                                                                                      |
|----------------------|--------------------------------------------------------------------------|------------------------|------------------------------------------------------------------------------------------------------------------------------|
| Prevalence           | Percentage of people from key population who are living with HIV         | GARPR 1.10, 1.14 & 2.5 | Num: Number of people diagnosed with HIV
Denom: Number of people tested for HIV                                           |
|                      | Percentage of people from a key population diagnosed syphilis            | WHO O-3b               | Num: Number of people diagnosed with active syphilis
Denom: Number of people tested for syphilis                          |
|                      | Percentage of people from a key population diagnosed gonorrhea           | WHO O-3b               | Num: Number of people diagnosed with gonorrhea
Denom: Number of people tested for gonorrhea                               |
|                      | Percentage of people from a key population diagnosed chlamydia           | WHO O-3b               | Num: Number of people diagnosed with chlamydia
Denom: Number of people tested for chlamydia                               |
|                      | Percentage of people from a key population diagnosed Hepatitis B         | WHO O-3b               | Num: Number of people diagnosed with HBV
Denom: Number of people tested for HBV                                           |
| Awareness of status  | Proportion of key populations who are HIV positive and knew their status | WHO 4                  | Num: Number of people with HIV who have been diagnosed and received their results
Denom: Number of people living with HIV |
| Enroll PLHIV in care | Proportion of key populations with HIV enrolled in HIV care (WHO 1.3)    | 1.6b                   | Num: Number of people with HIV who have been enrolled in HIV care
Denom: Number of people diagnosed with HIV              |

Programmatic Mapping and HIV/STI Prevalence Study among Key Populations in Angola

| Cascade Step    | Indicator                                                                                                                                                          | Indicator #      | Measure                                                                                                                                                                                                         |
|-----------------|--------------------------------------------------------------------------------------------------------------------------------------------------------------------|------------------|-----------------------------------------------------------------------------------------------------------------------------------------------------------------------------------------------------------------|
|                 | Proportion of KP with HIV currently enrolled in care among those who tested positive (WHO 1.3 & HCT_TST)                                                    | PMP 1.10         | Num: Number of people with HIV who were currently enrolled in HIV care

Denom: Total number of key populations who tested positive for HIV and who know their results                                     |
| Initiate on ART | Proportion of key populations currently receiving antiretroviral therapy (TX_CURR/CUSTOM INDICATOR)                                                         | PMP 1.12b        | Num: Number of people with HIV who are taking ART

Denom: Number of people diagnosed with HIV                                                                                                             |
|                 | Proportion of key populations currently receiving antiretroviral therapy among those who are currently enrolled in care

(TX_CURR/WHO 1.5 & WHO 1.3 & ART-2) | PMP 1.13         | Num: Number of people with HIV who are taking ART

Denom: Total number of key populations who tested positive for HIV, know their results and are currently enrolled in care                              |
| Sustain on ART  | Proportion of key populations known to be alive and on treatment 12 months after initiation of antiretroviral therapy (TXT_RE/WHO 1.6)                             | PMP 1.14b        | Num: Number of people with HIV who are taking ART for at least 12 months

Denom: Number of people diagnosed with HIV                                                                                      |
|                 | Percent of key populations with HIV known to be on treatment 12 months after initiation of antiretroviral therapy (TX_RET)                                         | PMP 1.15
Core | Num: Number of people with HIV who are taking ART for at least 12 months

Denom: Number of key populations in the ART start-up group initiating ART at 12 months prior to the end of the reporting period |

Programmatic Mapping and HIV/STI Prevalence Study among Key Populations in Angola

| Cascade Step        | Indicator                                                                                                                            | Indicator #      | Measure                                                                                                                                                                                                                   |
|---------------------|--------------------------------------------------------------------------------------------------------------------------------------|------------------|---------------------------------------------------------------------------------------------------------------------------------------------------------------------------------------------------------------------------|
| Suppress viral load | Proportion of key populations on antiretroviral therapy who are virologically suppressed (WHO 1.7, CUSTOM INDICATOR)                 | PMP 1.17b        | Num: Number of people with HIV on ART whose viral load is less than 1000 copies/ml

Denom: Number of key populations in the ART start-up group initiating ART at 12 months prior to the end of the reporting period |
|                     | Proportion of key populations on antiretroviral therapy who are virologically suppressed among those tested for viral load (WHO 1.7) | PMP 1.18         | Num: Number of people with HIV on ART whose viral load is less than 1000 copies/ml

Denom: Number of key populations on antiretroviral therapy tested for viral load in the reporting period                        |
|                     | Proportion of viral load tests with undetectable viral load (<1000 copies/ml) (TX_UNDETECT)                                          | PMP 1.19
Core | Number of viral load tests where the result is <1000 copies/ml

Denom: Number of viral load tests performed key populations on ART in the past 12 months prior to the beginning of the                              |
| Behavior            | Percentage of sex workers reporting the use of a condom with their most recent client                                                | 1.8; O-4a        | Num: Number of sex workers who reported that a condom was used with their last client

Denom: Number of people who reported having received money for sex in the last 12 months                                     |

| Cascade Step | Indicator                                                                                           | Indicator #      | Measure                                                                                                                                                                                                                                                |
|--------------|-----------------------------------------------------------------------------------------------------|------------------|--------------------------------------------------------------------------------------------------------------------------------------------------------------------------------------------------------------------------------------------------------|
|              | Percentage of men reporting the use of a condom the last time they had anal sex with a male partner | 1.12; O-4e, O-4g | 
Num: Number of male or transgender respondents who report condom use at last anal sex with a male partner in the last 12 months.
 
Denom: Number of male respondents who have had sex with at least one male partner in the past 6 months.
 |
| Stigma       | Percentage of key populations reporting stigma and discrimination                                   | O-5a             | 
Num: Number of people who report experiencing stigma or discrimination due to their sexual orientation, work or HIV status
 
Denom: Number of people interviewed
                                                                           |
|              | Percentage of people from key populations who have experienced discrimination by health workers     | NEEDS.7          | 
Num: Number of people who report experiencing discrimination by a health care worker
 
Denom: Number of people interviewed
                                                                                                                 |

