- To characterize and map high risk venues and events in each PPA where key populations meet new sexual partners.
- To characterize the men and women who visit high risk venues and events and women who work at these venues and identify gaps in HIV prevention services (HIV Testing and Counseling (HTC), condoms, and syndromic/etiologic STI management).
- To characterize key populations: sex workers, men who have sex with men and transgender women that visit venues in Luanda.
  - To estimate the prevalence of HIV, the percent of key populations with early HIV infection, among people with HIV the percent who is eligible for ART, and the percent virally suppressed.
  - To estimate the percent of people at each stage of the HIV continuum of care between HIV diagnosis and viral suppression.
  - To estimate the prevalence of syphilis, Hepatitis B, gonorrhoea, chlamydia and trichomoniasis
- To inform stakeholders about high-risk areas for HIV transmission
- To facilitate provincial action plans for HIV prevention among key populations

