| C23        | In the past 12 months, have you received information about HIV or AIDS from any health worker?                                                                                                   | Yes
1                                        | No
2     |
| C24        | Are you currently seeing a health worker for an HIV infection?                                                                                                                                   | Yes
1                                        | No
2     |
| C25        | Are you currently taking antiretroviral (ART) drugs to treat an HIV infection?                                                                                                                   | Yes
1                                        | No
2     |
| C26        | Now I have a few questions about HIV tests. Have you ever had an HIV test?
IF NO: GO TO C31.                                                                                                  | Yes
1                                        | No
2     |
| C27        | Has a medical provider ever told you that you are infected with HIV, based on an HIV test result? IF NO GO TO C29.                                                                               | Yes
1                                        | No
2     |
| C28        | Think about the first time a medical provider told you that you that you were infected with HIV. Did this occur in the past 3 months? Past 12 months? Or longer ago? IF LONGER AGO, SKIP TO C31. | Past 3 Months
Past 4-12 months
Longer ago | 1
2
3 |
| C29        | Have you been tested for HIV in the past 12 months?
IF NO, GO TO C31.                                                                                                                         | Yes
1                                        | No
2     |
| C30        | IF YES (C29=1) ASK: The last time you were tested, did you get your test result?                                                                                                                 | Yes
1                                        | No
2     |
| C31        | Some people have tried injecting drugs using a needle and syringe. Have you injected any non-prescription drug in the past 12 months?                                                            | Yes
1                                        | No
2     |

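### Four Table 4 indicators divide a numerator by a denominator that does not contain it, and Form C lacks the items needed for 12-month ART retention and several coverage rows

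*Protocol*

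**What the plan says.** Table 4 (Protocol, section VIII.B) lists the indicators to be estimated, and section VIII.B makes the HIV testing and treatment cascade a study objective. Four rows matter here.

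- **1.3b (Test people).** Numerator: "Num: Number of people tested for HIV who receive their results". Denominator: "Denom: Estimated number of key population living with HIV in the program geographic area".
- **PMP 1.15 (Sustain on ART).** Numerator: "Num: Number of people with HIV who are taking ART for at least 12 months". Denominator: "Number of key populations in the ART start-up group initiating ART at 12 months prior to the end of the reporting period".
- **PMP 1.17b (Suppress viral load).** The numerator is everyone with HIV on ART whose viral load is below 1000 copies/ml. The denominator is the same start-up group as in PMP 1.15.
- **Condom use at last anal sex.** The numerator counts male or transgender respondents over the last 12 months. The denominator reads "Denom: Number of male respondents who have had sex with at least one male partner in the past 6 months".

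Under Step 4 of section VI.C, Form C (Appendix 4) is the single questionnaire for venue patrons and workers. Its only item on ART use is C25: "Are you currently taking antiretroviral (ART) drugs to treat an HIV infection".

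**The concern.** A proportion needs its numerator to be a subset of its denominator. In these four rows it is not, so the result has no fixed upper bound and no clear meaning.

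Row 1.3b also conflicts with the rest of the table. Its title describes a share of key populations, not of people with HIV, and it cross-refers to GARPR 1.9 and 1.13. An earlier Table 4 row defines those same codes over all respondents.

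The start-up-group denominator in PMP 1.15 and 1.17b is a clinic cohort, which a cross-sectional venue survey does not enumerate.

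Separately, an indicator whose source question is never asked cannot be produced later by any analysis plan.

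**Working it through.** The protocol gives no numerical value for these indicators, so there is no figure to reproduce. I checked whether each numerator lies inside its denominator, worked out how far the ratio can go, and compared Table 4 with Form C items C1–C39.

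**1.3b.** Inputs: 6,236 men who have sex with men in Luanda and HIV prevalence 3.8% to 10.5% (section IV); 600 to be interviewed (section VI.C Step 4 and section VI.E).
- Living with HIV: 6,236 × 0.038 = 237; 6,236 × 0.105 = 655.
- If all 600 are tested and get results: 600/237 = 253%; 600/655 = 92%.
- This sets a survey count against a citywide estimate. If both parts are population counts, the indicator equals testing coverage divided by prevalence, so it passes 100% once coverage exceeds 3.8% to 10.5%. An assumed coverage of 30% gives 0.30/0.038 = 789% and 0.30/0.105 = 286%.
- With all respondents as denominator, the same survey gives 600/600 = 100%, the natural maximum.

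**PMP 1.15.** Assume equal ART starts each year and annual retention r. The numerator collects every earlier cohort, while the denominator is one cohort. With three yearly cohorts the ratio is r + r² + r³.
- r = 0.6: 0.600 + 0.360 + 0.216 = 118%.
- r = 0.9: 0.900 + 0.810 + 0.729 = 244%.
- The quantity intended, retention of one cohort at 12 months, would be 60% and 90%.

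**PMP 1.17b.** The numerator also includes people who started within the past year. With suppression s, the ratio is s(1 + r + r² + r³).
- r = 0.6, s = 0.6: 0.6 × 2.176 = 131%.
- r = 0.8, s = 0.8: 0.8 × 2.952 = 236%.
- With only one earlier cohort and r = s = 0.6, it is 0.6 × 1.6 = 96%, so values below 100% are possible.

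**Condom row.** Assume 600 men and 200 transgender women, all with a male partner in 12 months. Let c be the share reporting condom use and f the share with a male partner in 6 months.
- Transgender women left out of the denominator: 800c/(600f). For c = 60%, f = 80%: 480/480 = 100%. For c = 70%, f = 80%: 560/480 = 117%.
- Transgender women counted as male respondents: 800c/(800f). For c = 60%, f = 80%: 480/640 = 75%. This exceeds 100% only when c > f.
- Either way the row does not return the assumed 60%, because the recall windows differ.

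**Form C against Table 4.**

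| Needed by | Item required | Nearest Form C item |
|---|---|---|
| PMP 1.14b, PMP 1.15, denominator of PMP 1.17b | ART start or duration | C25, current use only; C28 dates diagnosis, not ART |
| CCP-3/CCP-5, PKG-2 | Free lubricant received | None; Form B lubricant items describe the venue |
| SRH-4, PKG-2 | STI screening in 12 months | C18B, care sought for symptoms only |
| GARPR 1.7/1.11/2.1 | Knows where to get a test | None |

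**Rows that do work.** The GARPR 1.9 & 1.13 testing row is nested and drawn from C29 and C30. Respondents first told of their infection more than 12 months ago skip both items, so they need a coding rule. PMP 1.18 is nested and drawn from C25 plus the viral load result. Awareness of status, current care (PMP 1.10) and current ART (PMP 1.12b) are also properly nested.

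**The case against.** The strongest reply is that the cascade is not broken. A reader might infer from the four faulty rows that the testing, retention and suppression steps are all lost. The documents do not support that: testing has a sound row in GARPR 1.9 & 1.13, and suppression on ART has one in PMP 1.18. Only 12-month retention is left without a usable row. This part of the objection stands and limits the point.

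Three other strong readings also go too far.

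- **Suppression among everyone with HIV.** Section V asks for "among people with HIV the percent who is eligible for ART, and the percent virally suppressed", and Table 4 has no such row. But the Summary (section II) frames suppression among people receiving ART, which PMP 1.18 serves, and viral load is already planned for consenting HIV-positive participants. This is a mild mismatch, not a missing analysis.
- **C10A.** It asks about the last male partner rather than last anal sex, but it directly follows C10 on anal sex with a man. That is too thin to count as a defect.
- **Values must exceed 100%.** They can, but need not: 1.3b gives 92% at the upper prevalence. The condom figure depends on whether transgender women count as male respondents. The specimen-collection text in section VI.C groups them with male participants, although the numerator of the row itself lists them separately.

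It can also be said that Step 1 of section VI.C allows the data-collection formats to be adapted and piloted, and that the Cabinda questionnaire (Appendix 5) is not shown. Both are true. The Form C gaps are therefore claimed only for PLACE and for the form as written; nothing in the protocol commits to adding these items.

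**Conclusion.** The point holds. Four Table 4 rows (1.3b, PMP 1.15, PMP 1.17b and condom use at last anal sex) are wrong as stated because the numerator is not contained in the denominator. The size for 1.3b, 92% to 253%, rests on the protocol's Luanda figures and on all 600 men being tested and getting results. The sizes for the other three rest on assumed retention, suppression, condom use and partner activity, and only show how far the ratios can drift.

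For the PLACE survey, Form C as written cannot supply PMP 1.14b, PMP 1.15, the stated denominator of PMP 1.17b, CCP-3/CCP-5, SRH-4, PKG-2 or GARPR 1.7/1.11/2.1. Twelve-month retention and those coverage rows are lost; testing and suppression on ART are not. Severity: should-fix.

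**What to change.** In Table 4:
- **1.3b:** use key-population respondents as the denominator, or delete the row as a near-duplicate of GARPR 1.9 & 1.13.
- **Condom row:** use the same people and the same 12-month window in both parts, and say whether transgender women are included.
- **PMP 1.15:** redefine as the share currently on ART among respondents who report starting ART at least 12 months ago. Label it a survey measure among survivors reached at venues. It misses deaths and people who no longer attend, so it will overstate cohort retention.
- **PMP 1.17b:** drop it in favour of PMP 1.18, or restrict both parts to respondents on ART for at least 12 months who have a viral load result.
- **Optional:** report viral load below 1000 copies/ml among all HIV-positive participants with a result, to match the section V objective.

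In Form C, add four or five questions: ever started ART and when, free lubricant in the past 12 months, STI screening in the past 12 months, and whether the respondent knows where to get an HIV test.

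The cost is table edits and about 1–2 minutes per interview, provided the change is made before fieldwork.
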